## Abstract

**Background:**

Loneliness affects up to 42% of long-term care residents and is associated with poor health outcomes. Humanoid robot interventions hold promise for reducing loneliness and decreasing barriers to social interaction in long-term care settings, such as the current COVID-19 safety measures in many countries, limited mobility, and poor health. We present a protocol describing an assessor-blinded randomized controlled trial comparing the effects of a humanoid robot intervention to treatment as usual, on loneliness and mental health outcomes in long-term care residents.

**Methods:**

Seventy-four (*n* = 74) older adults experiencing loneliness in 3 long-term care homes will be randomized 1:1 to an 8-week, twice a week social intervention with the Grace humanoid robot vs. a treatment as usual active control. We will assess change (baseline to week 8) in (1) loneliness (primary outcome), (2) depression severity, and (3) stress (secondary outcomes), as well as (4) other exploratory outcomes: anxiety, quality of life and reduction in acute healthcare utilization. We will also assess the feasibility and acceptability of the intervention using qualitative methods.

**Discussion:**

The proposed study will assess the effects of a social robot on loneliness and other mental health outcomes, as well as the feasibility of the intervention in older adults living in long-term care settings.

**Trial registration:**

NCT05423899.

## Introduction

Loneliness in long term care homes (LTC) is a worldwide epidemic, affecting up to 42% of the resident population compared to 10% of community-dwelling older adults (1), resulting in over $6.7 billion in direct costs annually in the U.S. alone (2). Loneliness is associated with poor mental health outcomes, such as increased stress, anxiety, and poor quality of life, and is considered both a symptom and a trigger for mental health conditions such as depression. Older adults are particularly vulnerable to loneliness due to circumstances associated with aging, such as losses of relationships, bereavement, medical comorbidities, retirement, decline in physical and cognitive function, and changes in living environments (3).

Mental health conditions in older adults are often managed with pharmacological treatment, with over 25% of lonely older adults being prescribed medications such as sedatives, opioids, antidepressants, and benzodiazepines (4). Pharmacological treatments are ineffective in up to 50–80% of older adults (5) and are often accompanied by adverse effects leading to discontinuation in as many as 30% of individuals (6). Psychotherapies, such as talk therapy, can be used as adjuncts or alternatives to pharmacotherapy (7) but require specialized therapists who are challenging to access, with waiting lists up to 12 months in Canada (8). These interventions are also administered one-on-one, which makes it a human-resource intensive and costly intervention. Loneliness in LTC homes is sometimes mitigated through recreational and group activities, however due to low staff-to-resident ratios as well as funding shortages and social distancing restrictions, these activities are often limited and the first to be defunded (9). There is thus an urgent need to test potentially effective, acceptable, and feasible behavioral interventions.

Social robots targeting loneliness are a promising intervention with growing evidence of having positive effects in older adults' mental health (10, 11). However, there is limited research on human-like robot interventions in older adults; over 70% of studies focus on pet robots, and only 11% on social/humanoid robots (12). Studies focusing on socially assistive humanoid robots have been mainly conducted in individuals with dementia (13, 14). Participants developed feelings of trust toward the robot, experienced reduced anxiety following interactions with the robot (13) and reported positive attitudes toward a long-term companionship with the robot (14). These case studies included ≤ 10 participants and did not include control groups. While preliminary findings are promising, there are no RCTs investigating the effects of a humanoid robot intervention on mental health outcomes in older adults. This study will assess the effectiveness, acceptability, and feasibility of the Grace humanoid robot vs. treatment as usual (TAU; group activities in the LTC) on symptoms of loneliness, stress and depression, as well as anxiety, quality of life and reduction in acute healthcare utilization.

## Methods

### Study design

This is a two-arm, assessor-blinded Randomized Controlled Trial (RCT) with 74 planned participants, examining an 8-week, 2 sessions per week, 30-min/session humanoid robot interaction intervention vs. treatment as usual (TAU) control group, in older adults who experience loneliness living in three LTC homes in Montreal, Quebec and Ottawa, Ontario, Canada.

### Interventions

#### Grace robot

The Grace robot was designed by Awakening Health/Hanson Robotics for healthcare settings and to interact with the elderly and those isolated by the COVID-19 pandemic (15). Grace is a robot with a human-like appearance, which can move, actively listen, engage in conversation and react appropriately to human emotions. Intervention activities will mostly consist of active listening and general discussions about topics of interest (e.g., hobbies, music). The participant will also have the option of other types of interactions with the robot, including robot-led meditation, robot-led light exercise, listening to music and singing. Because loneliness is a subjective experience and does not have a standardized solution, this is a personalized intervention approach (16). We anticipate that each older adult participant will have different needs and wishes when interacting with the robot, which will allow for a more natural interaction with the robot.

#### Treatment as usual

The treatment as usual active control group will not receive the robot intervention. We have deliberately chosen the participating LTC homes due to their high frequency of social interactions for their clients as part of their routine care (e.g., one-on-one and group activities, family interaction, exercise groups) compared to most LTC homes settings, making TAU an active control.

### Participants

We will recruit 74 participants from three LTC homes in Montreal and Ottawa in 12–15 months. The inclusion and exclusion criteria for participation in this study are outlined in Table 1.

**Table 1 T1:** Eligibility criteria.

**Inclusion criteria**	**Exclusion criteria**
(1) Aged ≥60 years old	(1) Do not speak English
(2) Living in a LTC home setting in Montreal	(2) Inability to provide consent
(3) Cognitively healthy, have mild cognitive impairment (MCI) or mild dementia (MMSE score of >20/clinical opinion of LTC homes staff members)	(3) Moderate to severe dementia (MMSE score <18/diagnosis of moderate-severe dementia/clinical opinion of LTC homes staff members)
(4) Able to provide consent	(4) Significant hearing loss
(5) Loneliness UCLA-3 (17) score of ≥ 6 or more (moderate-severe loneliness).	(5) Acutely unstable medical illnesses, including delirium, acute cerebrovascular/cardiovascular events within the last 6 months; having a terminal medical diagnosis with prognosis of < 12 months
	(6) High suicide risk (e.g., active suicidal ideation and/or current/recent intent or plan).

#### Randomization

Participants will undergo stratified 1:1 randomization [strata: site and baseline cognition (normal vs. MCI/dementia)] to the intervention or active control group to account for unequal numbers of participants and differential severity of cognitive impairments between sites. To maintain allocation concealment, participants will be asked to refrain from disclosing their allocation into either the intervention group or the treatment-as-usual group to other residents until data collection is completed.

### Outcomes

All primary, secondary, and exploratory data will be collected at baseline and 8-weeks (primary study endpoint). The total time required to complete each time point assessment is 30–40 min.

#### Primary outcome

Loneliness as measured by the Revised UCLA 20-item Loneliness Scale (18) at baseline vs. 8–weeks (primary study endpoint), a commonly used validated scale to screen for loneliness.

#### Secondary outcomes

Secondary Outcome A: Stress, as measured by the Perceived Stress Scale [PSS; (19)], a 14-item scale used to measure the degree to which life events are experienced and appraised as stressful.

Secondary Outcome B: Depression, as measured by the Patient Health Questionnaire [PHQ-9; (20)], a 9-item self-report questionnaire used to diagnose depression and assess symptom severity.

#### Exploratory outcomes

Anxiety and quality of life, as measured by Generalized Anxiety Disorder-7 (GAD-7) (21), EQ-5D-5L (22), respectively. We will also look for indications of a reduction in acute healthcare utilization (number of hospitalizations and emergency room visits) at 8 weeks post-intervention. Moreover, participant experiences and acceptability with the robot will be measured using qualitative methods (semi-structured interviews). We will also note whether feasibility outcomes have been met, wherein a) >50% of eligible participants will consent, b) recruitment goals are met during the study period (*n* = 74), and c) rate of attrition is <20% (dichotomous “yes/no”).

### Statistical analyses

Descriptive statistics will be run with continuous variables summarized using means and standard deviations, and categorical variables summarized using counts and proportions. Primary analyses for all quantitative outcomes including the primary, secondary and exploratory outcome measures (e.g., UCLA loneliness score, PHQ-9 score, GAD-7 score) will be compared between intervention and control groups, controlling for baseline scores using linear mixed models (SAS Institute, Cary, NC). For qualitative data, thematic analysis will identify and code central themes, using NVivo software (ver.10).

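### The linear mixed model rule takes in the sparse hospitalization and emergency visit counts, and their stated time window conflicts with the week-8 assessment schedule (minor)

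*Protocol article*

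**What the plan says.** All places are in the protocol article.

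- **Statistical analyses** sets one rule for "Primary analyses for all quantitative outcomes including the primary, secondary and exploratory outcome measures": the arms are compared "controlling for baseline scores using linear mixed models (SAS Institute, Cary, NC"). The examples given are scale scores. No other quantitative model is named and no outcome is exempted.
- **Exploratory outcomes** lists, beside the anxiety and quality-of-life scales, "acute healthcare utilization (number of hospitalizations and emergency room visits) at 8 weeks post-intervention".
- **Study design** describes the trial as "examining an 8-week, 2 sessions per week, 30-min/session humanoid robot interaction intervention".
- **Outcomes** states: "All primary, secondary, and exploratory data will be collected at baseline and 8-weeks (primary study endpoint").
- **Abstract, Methods** opens its outcome list with "We will assess change (baseline to week 8) in (1) loneliness (primary outcome") and puts utilization in item (4) of that list.

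**The concern.** There are two separate problems with one exploratory outcome.

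**Model.** A linear mixed model with no stated link or distribution assumes normal residuals with constant variance. Event counts over 8 weeks in about 30 people per arm are likely to be mostly zero and right-skewed, with a variance that depends on the mean. A mean difference with a symmetric interval describes such data badly, and one resident with several visits can carry much of the estimate. The Power analysis section says the results will feed power calculations for a confirmatory trial, so the quality of estimates matters even in a pilot.

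**Window.** A count has no meaning without its period. As written, someone abstracting records could count events during the intervention, in the 8 weeks after it, or both.

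**Working it through.** **Window, by comparing the text.** The intervention lasts 8 weeks. Read literally, 8 weeks post-intervention is week 8 + 8 = 16. The Outcomes section collects all exploratory data at baseline and week 8, and the Abstract puts utilization under change from baseline to week 8. No assessment is scheduled after week 8, so the three statements cannot all hold.

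**Model: inputs.** The plan gives no figure for this outcome, so there is none to reproduce. The only input from the document is 60 completers (Power analysis), or 60/2 = 30 per arm at 1:1 allocation. Event rates and dispersion are assumptions. With baseline as a covariate and a single post-baseline assessment, the model is in essence an analysis of covariance, apart from any random effect.

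**How sparse the counts are.** Assume a negative binomial count with mean m and shape k. The expected number of events among 60 completers with no effect is 60 × m, and the share of residents with no event is (k/(k+m))^k. For k = 1 the share is 1/(1+m). The last two columns are simulated with a baseline-adjusted linear model (4,000 trials per setting).

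| m per 8 weeks | Events in 60 | Share with none | Type I error | Power for a halved rate |
|---|---|---|---|---|
| 0.05 | 3 | 95% | 2.9% | 3% |
| 0.10 | 6 | 91% | 4.3% | 7% |
| 0.20 | 12 | 83% | 4.2% | 13% |
| 0.40 | 24 | 71% | 4.4% | 22% |

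**Interval coverage.** Pooled-variance 95% interval, 30 per arm, 20,000 simulated trials per setting:

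| Means, TAU vs robot | Shape k | Coverage |
|---|---|---|
| 0.3 vs 0.1 | 0.3 | 91.5% to 92.2% over repeated runs |
| 0.3 vs 0.1 | 1 | 94.0% |
| 0.3 vs 0.1 | Poisson | 94.4% to 94.7% over repeated runs |
| 0.3 vs 0.15 | 1 | 94.7% |
| 0.3 vs 0.2 | 0.3 | 94.9% |
| equal, 0.1 to 0.3 | 0.3 | 95.6% to 96.4% |

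Over all settings checked, from no effect to a threefold reduction, coverage runs from about 91.5% to 96.7%. More extreme pairings within the same ranges fall lower: 0.3 vs 0.05 with k = 0.3, a sixfold reduction, gives about 89%.

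**Where the misses fall.** In one run of 0.3 vs 0.1 with k = 0.3, coverage was 91.8%. The 8.2% of misses split into 7.7% that understate the true reduction and 0.5% on the other side. Expected events are 30 × 0.3 = 9 and 30 × 0.1 = 3. The resident with most events supplies a median of one third of the control-arm events.

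**Can a standard rate ratio fail?** The chance that an arm of 30 has no events is (k/(k+m))^(30k). With k = 0.3 this is (0.3/0.4)^9 = 0.075 at m = 0.1 and (0.3/0.35)^9 = 0.250 at m = 0.05. For 0.1 vs 0.05, the chance that at least one arm has none is 0.250 + 0.075 − 0.250 × 0.075 = 0.306. A Wald rate ratio then has no finite interval, so an exact fallback is needed.

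**The case against.** **The counts may never have been meant for this model.** The examples in the Statistical analyses section are all scale scores, the adjustment is for baseline scores, and a visit count has no score. The Exploratory outcomes section says only that the team will look for indications of a reduction, which could be descriptive. A condensed article may also leave the distribution of an exploratory count to a fuller document. This lowers the weight of the point but does not remove it. The article does not leave the choice open: it states a rule for all quantitative outcomes, names the exploratory ones, and makes no exception.

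**The window may be loose wording for week 8.** That is the likeliest meaning. A reader might infer that counts will actually be gathered over weeks 9 to 16. Nothing in the document supports this, since no contact is scheduled then. What stands is a conflict in the text that needs reconciling.

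**Stronger readings that do not hold.**

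- A reader might infer that the linear model gives false positives or generally invalid intervals. Type I error stays below 5% in the settings checked, and coverage is at or above nominal when there is no effect.
- A reader might object that interval limits imply negative visit rates. The model estimates a difference, which may be negative. The same feature appears with Poisson data whose coverage is close to nominal, so it reflects few events rather than miscoverage.
- A reader might argue that Table 1, by excluding "acute cerebrovascular/cardiovascular events within the last 6 months", holds baseline use artificially low. That exclusion does not cover all hospital use, the document gives no figure for its effect, and both randomised arms pass the same filter. It does not bias the between-arm comparison.

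**Conclusion.** The point stands as a minor one. The stated rule covers the hospitalization and emergency visit counts and suits them poorly, and their stated window contradicts the Outcomes section and the Abstract. The cost is to estimation: coverage of about 91.5% to 96.7% in the settings checked, with misses that tend to understate a true reduction, and a summary that one resident can sway. These figures rest on assumed rates, effects and dispersion, because the protocol gives none. No conclusion about the primary or secondary outcomes is affected, and no decision is tied to this outcome.

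**What to change.** - Restrict the linear mixed model to the scale scores.
- Define utilization as the number of hospitalizations and emergency room visits from randomisation to week 8, and use that wording in the Exploratory outcomes section so that it agrees with the Outcomes section and the Abstract.
- Compare the arms by a Poisson or negative binomial rate ratio with a log person-time offset. When events are few or an arm has none, use an exact method: an exact conditional rate ratio, or an exact comparison of any event versus none.
- Report the result as an exploratory between-arm estimate with its interval.

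This costs a few sentences and no extra visit; the person-time offset needs each resident's time under observation. The Ethics statement says recruitment had not started, so the change comes early. The downside is that the interval will be wide, and no model gives useful power with so few events.

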#### Power analysis

We estimate a total sample size of 74 participants recruited and randomized, with 60 study completers, taking into account a likely 20% attrition rate (loss to follow-up, not tolerating the intervention) based on our previous experience with RCTs (23–25). In this study, 74 participants will be randomized to either the treatment group or control group, with each having *n* = 37. On repeated measures ANOVA, 60 study completers will allow us to observe an effect size of 0.34 at two-tailed alpha = 0.05 and Power (1-Beta) = 0.8 (cite G^*^Power software). As this is a pilot study, results will be used for power calculations in order to assess an appropriate sample size for a future larger confirmatory RCT.

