#### Subgroup analyses

##### Sex-based subgroup analysis

We will complete a subgroup analysis reporting main outcomes in men and women, respectively. Sex, along with other baseline characteristics, will also be included as covariates in statistical models to capture their effects on outcomes. We will conduct subgroup analyses on primary outcome in patients stratified by site.

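### The primary model names neither stratification factor and its covariate set is left open; if site and cognition are omitted and prognostic, some precision is forgone

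*Protocol article*

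**What the plan says.** Under Randomization, the protocol article sets the "strata: site and baseline cognition (normal vs. MCI/dementia" and gives the reason for stratifying: "to account for unequal numbers of participants and differential severity of cognitive impairments between sites". Under Participants there are three homes, so the design has up to six strata.

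Under Statistical analyses, the arms are compared on all quantitative outcomes, including the primary one, "controlling for baseline scores using linear mixed models". The baseline score is the only covariate named in that section.

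Under Sex-based subgroup analysis, a second statement on covariates appears: "Sex, along with other baseline characteristics, will also be included as covariates in statistical models to capture their effects on outcomes". The other characteristics are not listed, and the models concerned are not identified. Site is named in the analysis text only as a subgroup variable: "We will conduct subgroup analyses on primary outcome in patients stratified by site". Baseline cognition is not named in the analysis text at all.

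The Power analysis section relies on repeated measures ANOVA with "two-tailed alpha = 0.05", and mentions no strata or covariates.

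**The concern.** Stratified allocation balances the arms on site and cognition, so the treatment estimate does not vary from those sources. A model without the factors still counts their variance as residual noise. If they are prognostic, the reported standard error then exceeds the true variability of the estimate. Confidence intervals are too wide, the test rejects less often than 5% under the null, and precision secured at randomisation is not used. With about 60 completers expected, that precision is worth having.

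The results are also meant to feed the power calculation of a later confirmatory trial. A residual variance taken from a model without prognostic strata would be larger than the one an adjusted analysis would face.

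The second issue is separate. Covariates are described in two places with different content, one of them open-ended. A reader cannot tell which model gives the primary result, and several adjusted estimates would be compatible with the text.

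**Working it through.** **Inputs from the protocol article.** 74 randomised 1:1, 60 completers, two-sided alpha 0.05, power 0.80, effect size 0.34 (Power analysis); three sites and two cognition levels (Participants, Randomization).

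**Input not in the documents.** R2, the share of outcome variance left after the baseline score that site and cognition explain. Assumed range: 0 to 0.30.

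**The plan's own figure.** Take 0.34 as Cohen's f for the between-group test of a repeated measures ANOVA with N = 60, m = 2 time points and within-person correlation rho. Then lambda = f²·N·m / (1 + (m−1)·rho), with 1 and 58 degrees of freedom. At rho = 0.7, lambda = 0.1156 × 120 / 1.7 = 8.16 and power is 0.802, which agrees with the stated 0.80. The article states neither the metric nor rho. At rho = 0.5 the same test gives 0.849; the group-by-time interaction gives above 0.95 at every rho tried. For attrition, 60 / 0.8 = 75 against 74, which is close enough. The reproduction uses no strata, so 0.80 does not depend on adjusting for them.

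**Approximate cost of omission.** Under balanced strata the model without them overstates the standard error by 1/√(1−R2), and its true two-sided error is about 2·(1 − Φ(1.96/√(1−R2))).

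- R2 = 0.10: 1/√0.90 = 1.054, true alpha about 0.039.
- R2 = 0.20: 1/√0.80 = 1.118, true alpha about 0.028.

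**Simulation.** 8,000 trials per row with n = 60, site shares 0.40/0.35/0.25, cognition split evenly, and permuted blocks of 4 within strata. The true effect was set at 2.8015 × 1.03 × √(4/60) = 0.745 post-baseline residual SDs, so that the baseline-only model has about 80% power at R2 = 0. Linear models with the baseline score alone were compared with models adding site and cognition.

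| R2 | mean SE, without / with strata | ratio | type I error, without / with | power, without / with | points forgone |
|---|---|---|---|---|---|
| 0 | 0.259 / 0.260 | 1.00 | 0.050 / 0.049 | 0.796 / 0.795 | about 0 |
| 0.05 | 0.260 / 0.254 | 1.02 | 0.044 / 0.048 | 0.806 / 0.821 | 1.5 |
| 0.10 | 0.260 / 0.247 | 1.05 | 0.037 / 0.047 | 0.815 / 0.842 | 2.6 |
| 0.20 | 0.260 / 0.233 | 1.12 | 0.031 / 0.049 | 0.836 / 0.884 | 4.8 |
| 0.30 | 0.260 / 0.218 | 1.19 | 0.020 / 0.049 | 0.840 / 0.917 | 7.8 |

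The ratios match the formula. At R2 = 0.20 the estimate from the model without strata has an empirical standard deviation of 0.236 against a mean reported standard error of 0.260, which shows the overstatement directly.

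**The case against.** The strongest objection is that this is a condensed article and a full covariate list may properly sit in the analysis plan, which is not shown. That would settle the matter if the article were silent on covariates. It is not: it states a model and then adds to it elsewhere, in terms that leave the primary model undetermined. The objection does limit the point to clarifying and improving a stated model.

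Several stronger readings are tempting, and the documents do not support them.

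- *The primary model adjusts only for the baseline score.* A reader might infer this from the Statistical analyses section. However, baseline cognition falls naturally among further baseline characteristics, and a linear mixed model could carry site as a random effect. If both strata are in the model, the loss disappears.
- *Power is certainly lost.* The loss requires site and cognition to predict week-8 loneliness beyond baseline loneliness. The article says that cognitive severity differs between sites; it gives no figure linking either factor to loneliness.
- *The trial falls below its stated power or inflates false positives.* Neither follows. The 0.80 names no strata; in the simulation the model without them stays at about 0.80 or above, and its error is on the conservative side.
- *The open covariate list widens standard errors.* It does not. Its risk is choice of model after the data are seen.
- *The mixed model must be replaced by ANCOVA.* The remedy does not need this; the strata can be added to whichever model is fitted.

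**Conclusion.** The point holds conditionally and is worth acting on. The stated primary model does not name the factors used to stratify, and the text does not settle whether they are included. If they are omitted and explain 5% to 20% of the post-baseline variance, the standard error is about 2% to 12% too wide and about 1.5 to 5 power points are forgone. At zero there is no loss.

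These sizes rest on the assumed R2, on additive strata effects, on strata close to balanced among completers, and on a simulated effect calibrated to about 80% power, since the article gives neither the metric of its effect size nor a correlation. The open-ended covariate set is a separate weakness in pre-specification and does not depend on R2.

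**What to change.** In Statistical analyses, name site (three levels) and baseline cognition (normal vs MCI/dementia), with the baseline score, as covariates in the primary model. List in advance any further covariate, such as sex, or drop the unlisted characteristics from the primary analysis and confine them to analyses labelled supportive. Make the subgroup section agree with this, and fix it all before the data are seen.

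The cost is a sentence or two and three degrees of freedom (two for site, one for cognition). Both factors are already collected for randomisation. If they turn out not to be prognostic, the simulated price is negligible: power 0.795 with them against 0.796 without.
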